### 3.2. Brain MRI Analysis

Preprocessing for MRI data will use standardized pipelines: fMRIPrep v24.0 for T1 and resting-state fMRI (anatomical segmentation, motion correction, spatial normalization, and smoothing at 6 mm full-width half maximum), and QSIPrep v0.21 for DWI (eddy-current correction, bias-field correction, and tensor fitting).

Structural MRI, diffusion-weighted imaging (DWI), and resting-state fMRI will be analyzed to comprehensively characterize brain structure, white matter integrity, and intrinsic functional organization associated with anxiety and treatment response. Structural MRI will yield cortical thickness and gray matter volume measures; DWI will provide white matter microstructural indices, including fractional anisotropy and mean diffusivity; and resting-state fMRI will be used to derive functional connectivity, amplitude of low-frequency fluctuations, and regional homogeneity as candidate neurobiological features for group comparisons and predictive modeling.

Group-level comparisons will be performed between (i) healthy controls and anxiety participants and (ii) responders and non-responders using general linear models with age and sex as covariates. Multiple comparisons will be adjusted using the false discovery rate. Significant neural indices will be further examined as candidate predictive features in multimodal modeling.

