### 3.3. Predictive Modeling of Treatment Response

The primary objective is to develop machine-learning models that predict treatment response (≥40% PDSS reduction at 2, 6, and 12 months). Binary (responder vs. non-responder) and three-group models (healthy control, responder, non-responder) will be evaluated. Predictor features will include sociodemographic and psychiatric-history variables, clinical and psychometric scores, VR-derived behavioral indices, EEG/ECG features, 3D skeletal tracing, and neuroimaging markers. In most models, age and sex will be treated as basic covariates given their known influence on neural and behavioral measures. Lifestyle variables (e.g., education, smoking, alcohol use) and treatment-related clinical variables (medication use and psychotherapy) will be systematically recorded and incorporated either as covariates to adjust for treatment effects or as candidate predictive features, depending on the specific modeling objective and analytic context.

Predictor inclusion and feature reduction will be guided by a combination of theoretical relevance and empirical criteria. Candidate variables will undergo an initial screening based on prior literature and clinical interpretability. Dimensionality will then be reduced using data-driven feature-selection procedures, such as penalized regression methods (e.g., LASSO) or feature-importance-based ranking, with the number of retained features determined by model performance and stability rather than a predefined target. Variables exhibiting substantial multicollinearity (e.g., variance inflation factor > 5), redundancy, or consistently low contribution across cross-validation folds may be excluded prior to model fitting.

All features will be standardized, and missing values handled using multiple imputations by chained equations or similar robust approaches. Depending on data characteristics, dimensionality-reduction techniques (e.g., principal component analysis) may be applied before model fitting.

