The full multimodal analytic workflow supporting these predictive models is summarized in Figure 3. This figure outlines the end-to-end structure of the pipeline, beginning with modality-specific preprocessing (sociodemographic/clinical variables, VR behavioral data, EEG/ECG signals, 3D-skeletal tracking, and MRI), followed by a multimodal feature-integration stage, and culminating in supervised-learning models and validation procedures. This framework visually captures how heterogeneous data streams are harmonized into a unified dataset for treatment-response prediction and how complementary neurobiological profiling analyses interface with the main machine-learning pipeline.

Various supervised-learning algorithms—such as logistic regression, support-vector machines, random forests, or gradient-boosting methods (e.g., XGBoost, CatBoost)—may be compared. Model performance will typically be evaluated through k-fold or nested cross-validation, using metrics such as area under the curve, F1 score, and balanced accuracy. Model interpretability will be explored through feature-importance or SHapley Additive exPlanations-value analyses. All analytic pipelines will be version-controlled to ensure reproducibility.

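### The plan permits feature selection on the outcome outside the cross-validation loop, which can inflate the reported AUC

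*Protocol article*

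**What the plan says.** Section 3.2 lists two group comparisons of the MRI indices. The second is "ii) responders and non-responders using general linear models with age and sex as covariates". It adds "Multiple comparisons will be adjusted using the false discovery rate", without a level, and then passes the result on: "Significant neural indices will be further examined as candidate predictive features in multimodal modeling".

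Section 3.3 predicts the same responder label. Its first filter does not use the outcome: "Candidate variables will undergo an initial screening based on prior literature and clinical interpretability". LASSO or importance ranking follows, "with the number of retained features determined by model performance and stability rather than a predefined target". Variables with "consistently low contribution across cross-validation folds may be excluded prior to model fitting". Several algorithms may be compared, and "Model performance will typically be evaluated through k-fold or nested cross-validation".

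Section 3.4 promises confidence intervals, variability across folds, calibration and 1000 bootstrap iterations. It does not say that any of these repeats the feature selection.

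**The concern.** Cross-validation estimates out-of-sample performance only if the held-out patients played no part in building the model. Two steps in the text can break this.

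- **The responder screen.** A group-level comparison is most naturally run on all patients. If its significant indices then enter the model, each held-out patient's outcome has already influenced the feature list. Nested cross-validation run afterwards does not repair this, because the screen lies upstream of both loops.
- **Pruning across folds before fitting.** Contribution summed over all folds draws on every patient. It is harmless only if the folds are the inner folds of a nested scheme.

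With plain k-fold, the folds that report performance may also settle the number of features and the algorithm.

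Prediction of response is the primary objective in section 3.3, and no external or held-out set would expose the optimism. A biomarker panel could look useful with little or nothing behind it.

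**Working it through.** **The plan's own figure.** The article states no expected AUC, so there is none to reproduce. The question is how far selection outside the folds could move it.

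**Inputs from section 2.7.** 145 patients, 20% dropout, 25% non-response, about 20 variables per model.

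- Analysable patients: 145 × (1 − 0.20) = 116
- Non-responders: 116 × 0.25 = 29

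Section 2.7 also speaks of 80 non-responders, but its own rate would need 80 / 0.25 = 320 analysable patients for that. The working uses 29.

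**Assumed, because the article is silent.** The number of candidate features, the FDR level (5%), the size of any true signal, five folds, and the classifier.

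**1. Top 20 features chosen by t-test on all data, then 5-fold cross-validation, pure noise (true AUC 0.50)**

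| Candidates | AUC, selection on all data | AUC, selection in-fold |
|---|---|---|
| 40 | 0.64 | about 0.50 |
| 100 | 0.77 | about 0.50 |
| 200 | 0.84 | about 0.50 |
| 500 | 0.89 | about 0.50 |

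With features correlated 0.3 in blocks (300 runs), the inflated figures are 0.70, 0.81 and 0.90 for 100, 300 and 1000 candidates, against 0.497 to 0.506 in-fold. With weak true signal (5 to 10 features at d = 0.5), they are 0.80, 0.89 and 0.93, against 0.65, 0.68 and 0.62 in-fold.

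**2. Pruning on contribution across folds, then cross-validation on the survivors, pure noise**

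- Lenient rule, dropping only features that LASSO picks in no fold (40 runs): 0.63 to 0.64 with 20 to 40 candidates, 0.75 with 100, 0.85 with 200.
- Strict rule, keeping features picked in at least three of five folds (60 runs): 0.81, 0.89 and 0.95 with 100, 200 and 500.

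The article does not define consistently low contribution, so both rules are assumptions.

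**3. FDR screen on all data, then cross-validation**

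Average inflation = P(any index passes) × (cross-validated AUC − AUC in new patients), counting an empty screen as no inflation. Correlation 0.3 in blocks, 300 runs per row.

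| Candidates | True signal | P(pass) | CV AUC if passed | New-patient AUC | Difference | Average |
|---|---|---|---|---|---|---|
| 100 | none | 0.07 | 0.724 | 0.505 | 0.219 | 0.015 |
| 300 | none | 0.04 | 0.739 | 0.503 | 0.236 | 0.009 |
| 1000 | none | 0.05 | 0.769 | 0.505 | 0.264 | 0.013 |
| 100 | 5 at d = 0.5 | 0.49 | 0.766 | 0.658 | 0.108 | 0.053 |
| 300 | 10 at d = 0.5 | 0.53 | 0.792 | 0.659 | 0.133 | 0.070 |
| 1000 | 10 at d = 0.5 | 0.40 | 0.789 | 0.645 | 0.144 | 0.058 |

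A second simulation with weaker signal (d = 0.4) gave 0.765 − 0.609 = 0.156 with 200 candidates and 0.771 − 0.597 = 0.174 with 500. An index passed in 21 to 29% of runs, so the average lies between 0.156 × 0.21 = 0.03 and 0.174 × 0.29 = 0.05.

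Ranking or pruning outside the folds is thus the larger hazard. The FDR route matters mainly when an index passes, which is also when a neural biomarker would be reported.

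**The case against.** A reader might infer that the plan commits to selecting predictors in the full sample before cross-validation, and that the AUC will therefore be strongly inflated. The documents do not support that.

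- The article never says that the whole sample is used or that the screen precedes validation. That order is the natural reading of section 3.2, not a stated rule.
- Section 3.2 does not say that only significant indices enter. It already names resting-state measures as candidates for both comparison and prediction. The Figure 3 caption describes the neurobiological profiling as parallel, and the non-MRI predictors do not pass through this screen.
- Pruning is optional, the first filter rests on literature, and nested cross-validation is a listed choice. Choosing the number of features on performance is ordinary tuning if done in an inner loop.
- The size depends on an unstated candidate count. With no true signal, the FDR route passes an index in only 4 to 7% of runs.
- Section 3.4 calls all analyses exploratory, and a condensed article may leave the placement of scaling and imputation to the full plan. Those steps are not outcome-based selection and are no evidence here.

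All of this stands, and it limits the size and certainty of the point. It does not remove it. The hand-off from the responder comparison and the pruning before fitting are affirmative text, not silence. Nothing confines either to training patients, and section 3.4 itself promises to prevent overfitting, which an exploratory label does not achieve.

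**Conclusion.** The point holds as a fault in what the plan permits. Following sections 3.2 and 3.3 in their natural order would let held-out patients influence the features on which they are then scored.

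If ranking is done on all data, noise alone can give an AUC of about 0.64 to 0.89 for 40 to 500 candidates, when the truth is 0.50. The FDR screen alone inflates by about 0.11 to 0.17 under weak signal when an index passes. Averaged over all runs it adds about 0.03 to 0.07 with weak signal and 0.01 to 0.02 with none.

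These figures rest on 116 patients with 29 non-responders and on the assumed candidate counts, signal strengths and selection rules. They show what could happen, not what will. If every outcome-dependent step is kept in-fold, the bias disappears.

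**What to change.** - **Section 3.2:** state that the responder versus non-responder comparison is descriptive and does not determine which indices enter the model.
- **Section 3.3:** state that all outcome-dependent steps (screening, ranking, pruning, number of features, tuning, choice of algorithm) are refitted within training folds only. Require nested cross-validation whenever features, tuning or algorithm are chosen on performance. Plain k-fold need not be banned: it is valid with a prespecified algorithm and all such steps in-fold.
- **Section 3.4:** state that the bootstrap repeats the whole pipeline, selection included.
- **Three-group model:** apply the same rule to the control versus anxiety comparison, which uses that model's labels. It does not use the response label, so it does not leak into the binary model.

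The cost is a few sentences and more computing time. Reported AUCs will be lower, and the change should be made before any model is fitted.

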### 3.3. Predictive Modeling of Treatment Response

The primary objective is to develop machine-learning models that predict treatment response (≥40% PDSS reduction at 2, 6, and 12 months). Binary (responder vs. non-responder) and three-group models (healthy control, responder, non-responder) will be evaluated. Predictor features will include sociodemographic and psychiatric-history variables, clinical and psychometric scores, VR-derived behavioral indices, EEG/ECG features, 3D skeletal tracing, and neuroimaging markers. In most models, age and sex will be treated as basic covariates given their known influence on neural and behavioral measures. Lifestyle variables (e.g., education, smoking, alcohol use) and treatment-related clinical variables (medication use and psychotherapy) will be systematically recorded and incorporated either as covariates to adjust for treatment effects or as candidate predictive features, depending on the specific modeling objective and analytic context.

Predictor inclusion and feature reduction will be guided by a combination of theoretical relevance and empirical criteria. Candidate variables will undergo an initial screening based on prior literature and clinical interpretability. Dimensionality will then be reduced using data-driven feature-selection procedures, such as penalized regression methods (e.g., LASSO) or feature-importance-based ranking, with the number of retained features determined by model performance and stability rather than a predefined target. Variables exhibiting substantial multicollinearity (e.g., variance inflation factor > 5), redundancy, or consistently low contribution across cross-validation folds may be excluded prior to model fitting.

All features will be standardized, and missing values handled using multiple imputations by chained equations or similar robust approaches. Depending on data characteristics, dimensionality-reduction techniques (e.g., principal component analysis) may be applied before model fitting.

The full multimodal analytic workflow supporting these predictive models is summarized in Figure 3. This figure outlines the end-to-end structure of the pipeline, beginning with modality-specific preprocessing (sociodemographic/clinical variables, VR behavioral data, EEG/ECG signals, 3D-skeletal tracking, and MRI), followed by a multimodal feature-integration stage, and culminating in supervised-learning models and validation procedures. This framework visually captures how heterogeneous data streams are harmonized into a unified dataset for treatment-response prediction and how complementary neurobiological profiling analyses interface with the main machine-learning pipeline.

Various supervised-learning algorithms—such as logistic regression, support-vector machines, random forests, or gradient-boosting methods (e.g., XGBoost, CatBoost)—may be compared. Model performance will typically be evaluated through k-fold or nested cross-validation, using metrics such as area under the curve, F1 score, and balanced accuracy. Model interpretability will be explored through feature-importance or SHapley Additive exPlanations-value analyses. All analytic pipelines will be version-controlled to ensure reproducibility.

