### 2.7. Sample Size and Power Considerations

This study is designed to identify predictive biomarkers of treatment response through multimodal data modeling in a prospective, observational framework. Since the primary goal is to develop prediction models rather than to test predefined hypotheses, traditional power calculations based on inferential statistics are not directly applicable.

For the cross-sectional comparison between the clinical anxiety group and the healthy control group, a medium effect size (Cohen’s d = 0.5) was assumed based on prior neuroimaging meta-analyses [32]. This yielded a minimum required sample size of 36 participants per group to achieve 80% power at a two-sided α = 0.05. Accounting for a 10% attrition rate, the control group target was set at 40 participants.

Sample size planning for predictive modeling was based on guidelines by Riley et al. [33], which recommend ensuring a sufficient number of events per predictor parameter to reduce the risk of model overfitting. Although the dataset includes numerous raw variables across clinical, behavioral, physiological, and neuroimaging domains, only a subset (~20 variables) will be used in each model following feature selection procedures. Assuming a non-response rate of 25% (the reported remission rate of 38–75% at 6 months) [34,35], at least 80 non-responders would be required to ensure four events per predictor. Accordingly, the clinical anxiety group was targeted at 145 participants to allow for a 20% dropout rate and ensure sufficient statistical power for model development.

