### 3.4. Statistical Considerations

All analyses will be exploratory and hypothesis-generating. Normality of data distributions will be verified using the Shapiro–Wilk test and residual diagnostics. If assumptions for parametric tests are violated, appropriate transformations or non-parametric alternatives will be employed. Potential covariates (age, sex, medication status, treatment type) will be included as needed. Missing data will be handled using multiple imputation or complete-case analysis, depending on the extent and mechanism of missingness.

To ensure generalizability, model interpretability, and prevention of overfitting, we will report confidence intervals, cross-validation performance variability, and model calibration statistics where applicable. Robustness checks (e.g., bootstrapping with 1000 iterations) will be performed to confirm model stability. All analyses will be implemented in R (version 4.3.1 or later) and Python (version 3.10 or later). The analysis code will be managed using a version-controlled repository (Git), and the final software environment, including package versions, will be documented to ensure reproducibility.

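### Section 3.3 permits plain k-fold cross-validation both to choose the algorithm and feature count and to report performance, which makes the reported performance optimistic

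*Protocol article*

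**What the plan says.** The primary objective in Section 3.3 is to develop models that "predict treatment response (≥40% PDSS reduction at 2, 6, and 12 months". Four parts of the plan bear on how such a model is chosen and judged.

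- **Algorithms.** Section 3.3 gives an open list, "such as logistic regression, support-vector machines, random forests, or gradient-boosting methods (e.g., XGBoost, CatBoost)—may be compared".
- **Number of features.** Section 2.7 expects that "only a subset (~20 variables) will be used in each model following feature selection procedures". Section 3.3 declines to fix the number: selection proceeds "with the number of retained features determined by model performance and stability rather than a predefined target". It also lets variables that contribute little across the cross-validation folds be dropped before fitting.
- **Validation and metric.** "Model performance will typically be evaluated through k-fold or nested cross-validation", "using metrics such as area under the curve, F1 score, and balanced accuracy". No visit and no metric is named as primary.
- **Safeguards.** Section 3.4 promises confidence intervals, the variability of cross-validated performance, calibration where applicable, and a bootstrap: "Robustness checks (e.g., bootstrapping with 1000 iterations) will be performed to confirm model stability". It also declares all analyses exploratory.

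The article describes no held-out or external test set.

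**The concern.** Plain and nested cross-validation are interchangeable only when nothing about the model is chosen by its cross-validated score. Once the algorithm or the feature count is chosen that way, the winner's k-fold score is the maximum of several noisy estimates and is biased upward. A confidence interval computed for the winner as if it had been the only candidate ignores that choice. Nested cross-validation avoids this because the choice is made in inner folds and the score comes from outer folds that played no part in it.

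This differs from screening features on the full data before cross-validation. The bias remains when every feature is ranked and standardised inside the training folds.

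The claim to have found predictive biomarkers rests on the cross-validated performance of these models. If that performance may include selection optimism, a modest AUC above 0.5 cannot be told apart from the effect of the search.

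**Working it through.** **Inputs from the plan (Section 2.7).** The clinical target is 145, with 20% dropout and 25% non-response.

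- Completers: 145 × 0.80 = 116.
- Non-responders: 116 × 0.25 = 29.

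The plan gives no figure for cross-validation error, so there is none to reproduce. Its requirement of 80 non-responders is 20 predictors × 4 events. The stated target and rates deliver 29. That is a separate sample-size point; here 29 is simply the number that the plan's inputs yield.

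**Assumptions, not in the plan.** The search has 4 learners × 4 feature counts (5, 10, 20, 40) = 16 candidates per visit, or 16 × 3 = 48 over three visits. Features are pure noise with respect to response. Response at the three visits has latent correlation 0.6. Validation is stratified 5-fold with feature ranking inside the training folds. The marker of apparent success is a lower 95% DeLong limit above 0.5 for the pooled out-of-fold AUC.

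**Null simulations.** Run A used 100 features in 5 correlated blocks; logistic regression, support-vector machine, random forest and gradient boosting; and 200 datasets. Run B used 200 noise features; ridge logistic, radial kernel, nearest neighbours and bagged stumps as stand-ins; and 400 datasets. Run C is a further null simulation of the same kind.

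| No true signal | Run A | Run B | Run C |
|---|---|---|---|
| Fixed model, one visit: lower limit > 0.5 | 8.0% | 6.8% | about 8–11% |
| Best of 16, one visit: mean AUC | 0.577 | 0.584 | 0.57 |
| Best of 16, one visit: lower limit > 0.5 | 30.5% | 32.2% | 25% |
| Best of 48, three visits: mean AUC | 0.639 | 0.640 | 0.63 |
| Best of 48, three visits: lower limit > 0.5 | 64.5% | 63.5% | 56% |

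The Monte Carlo standard error of the one-visit figure is √(0.305 × 0.695 / 200) = 3.3 points in run A and √(0.322 × 0.678 / 400) = 2.3 points in run B. The one-visit rate is 30.5/8.0 = 3.8 times the fixed-model rate in run A, 32.2/6.8 = 4.7 times in run B, and 25/11 to 25/8 = 2.3 to 3.1 times in run C.

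**Sensitivity.**

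- Run B was varied over visit correlation 0 to 0.9, 50 to 1000 features, 25% or 40% events, 116 or 145 patients, and 3 or 4 feature counts. The three-visit figure ranged from 54% to 66%.
- A variant with 10 folds and five other simple learners gave 31% (50 features) and 47% (200 features) at one visit, and 63% and 73% over three. The figures move with the search.
- Judged instead against the null 95th percentile of one fixed model (5% by construction), the best candidate exceeds it in 13% to 26% of datasets at one visit and 33% to 59% over three.

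**Effect of nesting (run B).** At one pre-named visit, nested cross-validation gives mean AUC 0.499 and a lower limit above 0.5 in 6.2%, much as for the fixed model (0.497 and 6.8%). If the best of three visits is then highlighted, nested cross-validation still gives 20.2%, and a fixed model 20.0%. Nesting removes the optimism from choosing the model, but not that from choosing the visit.

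**The case against.** Several points on the other side are sound.

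- **Nested cross-validation is already permitted.** The sentence can be read as intending it wherever tuning occurs. That reading is possible but not required: plain k-fold is offered on the same footing, and the qualifier *typically* loosens even that.
- **The analyses are exploratory, and the plan sets no AUC threshold or test against 0.5.** This is true and lowers the stakes. It does not make a selected AUC unbiased.
- **Feature count is tied to stability as well as performance, and comparing algorithms does not mean that only the winner is reported.** Both are correct. The plan permits the biased route; it does not commit to it.
- **Section 3.4 has safeguards.** Calibration, fold variability and a bootstrap for stability are useful. As written, none separates choosing from scoring, and the text does not say whether the bootstrap reruns the whole pipeline.
- **Part of the apparent-success rate comes from the interval itself.** A two-sided 95% interval should lie above 0.5 in about 2.5% of null datasets, yet the fixed model already gives 7% to 11%. The comparison with a fixed model is therefore the relevant one.
- **An article leaves detail to a fuller document.** The absence of a permutation test or a named algorithm would not be a finding by itself. The validation scheme, however, is stated here, and stated too loosely.

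A reader might infer that the plan would produce an apparently positive model about 65% of the time when there is no signal. The document does not support that. The figure needs a 48-candidate search whose size the plan does not give, a success criterion that it does not set, and a report of only the best visit. All three visits are listed as targets; no passage says that cross-validation picks among them.

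**Conclusion.** The concern holds in a limited form. Section 3.3 approves a route on which the same folds choose the algorithm and feature count and supply the reported performance, and Section 3.4 as written does not correct it. Under the plan's 116 patients and 29 events, no signal, and an assumed 16-candidate search at one visit, the AUC optimism is about 0.07 to 0.08. A lower 95% limit above 0.5 arises in about 25% to 32% of datasets, against about 7% to 11% for a pre-fixed model.

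The 54% to 66% figure applies only if the best of three visits is also singled out. About half of it comes from the lack of a primary visit, a related but distinct gap that nested cross-validation does not close. The direction of the bias is certain whenever performance chooses among candidates; its size depends on the assumed grid, learners and criterion. This should be changed, but it does not undermine the design of the study.

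**What to change.** In Section 3.3, replace the open choice of validation scheme with wording such as: *Nested cross-validation will be used whenever the algorithm, number of features, PCA step or tuning parameters are chosen by performance. All such choices, with imputation and scaling, are made inside the training folds, and only outer-fold performance is reported.*

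In the same section, name one primary visit and one primary metric, and state that results for all algorithms and visits will be shown, not only the best.

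A label-permutation reference for the primary pipeline would be a reasonable optional addition. Making the release of feature-importance or SHAP results conditional on it goes further than exploratory work needs.

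The cost is wording and computing time; no patients or data are added. Reported AUCs will be lower, and inner-loop choices will be less stable with about 29 events. With data collection planned through 2029, the change can be made before the final models are fitted.
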